#### Rectal compliance and sensitivity

Previous studies [29] with alosetron showed an increase in compliance from 5.9 (SD 1.3) to 9.8 (SD 1.2) ml/mmHg in 22 patients. We propose to study more patients to test correlation with symptoms, which typically requires much larger numbers, so we will aim to study 40 patients on each treatment.

### Recruitment

Patients with IBS-D will be identified at recruiting sites from outpatient clinics and lists of patients that have previously consented to be contacted for information on upcoming research studies by local investigators and research nurses. Potentially eligible patients with IBS-D will also be identified by primary care general practices and local pharmacies, working either as patient identification centres (PIC), or a source of trial advertising. The TRITON trial will also be advertised using posters and leaflets in electronic and paper form and distributed to relevant locations outside of the secondary care setting and will advise patients to visit the trial website for further information. Patients will be screened against the aforementioned inclusion and exclusion criteria and will be provided with trial information.

### Randomisation

Randomisation will be performed on a 1:1 basis to receive either ondansetron or placebo, and each patient will be allocated three bottles of trial medication, each with a unique IMP kit code. Minimisation will be used, in order to ensure treatment groups are well-balanced. The stratification factors are registering site and whether the patient has undergone mechanistic assessments.

### Blinding

As the trial is double-blind, neither the patient nor those responsible for their care and evaluation (treating team and research team) will know the allocation or coding of the treatment allocation. This will be achieved by identical packaging and labelling of both the over-encapsulated ondansetron and matched placebo. Each bottle of ondansetron/placebo will be identified by a unique kit code. Randomisation lists containing kit allocation will be generated by the safety statistician at the Clinical Trials Research Unit (CTRU) and sent to the clinical supply company, which will produce the kits and the code-break envelopes. Management of kit codes on the kit logistics application, which is linked to the 24-h randomisation system, will be conducted by the CTRU safety statistician in addition to maintaining the back-up kit-code lists for each site.

Access to the code break envelopes will be restricted to the safety statistician and designated safety team. Code breaks will be permitted in emergency situations, where treatment allocation knowledge is needed to optimise treatment of the patient. Any unblinded interim reports provided to the Data Monitoring and Ethics Committee (DMEC) will be provided by the CTRU safety statistician and the reports will be securely password-protected.

### Data collection methods

#### Primary outcome method

##### Responders

According to the FDA definition [28], a responder is a patient who records both a reduction in pain intensity (≥ 30% decrease from baseline in weekly average worst daily pain) and improvement in stool consistency (≥ 50% decrease in the number of days per week with ≥ 1 loose stool of BSFS [21] 6 or 7) for at least 6 weeks of the 12-week treatment period, which is recorded in the daily diary and text messages.

#### Secondary outcome methods

Daily diary entries will record stool consistency, worst abdominal pain, stool frequency, worst urgency of defaecation, use of rescue medication over 12 weeks of treatment, and the answer to the question “Overall, have you had satisfactory relief from your IBS symptoms in the past week?”. The same diaries will be used between visits 5 and 6 to determine if there are any persisting effects of the treatment. Questionnaire booklets at visits 3 and 5 will record IBS-SSS, SF-LDQ, IBS-QOL, and HADS.

#### Mechanistic outcome methods

Whole gut transit (*n* = 400) will be assessed at visits 3 and visit 5 by ingestion of radio-opaque markers 6 days before an abdominal x-ray, as previously described [27]. Serum will be sampled (*n* = 400) at visit 3 to genotype patients for polymorphisms in the *TPH1* gene. Stool samples (*n* = 400) will be collected and frozen by patients in their homes prior to randomisation and at visit 5 to assess for total faecal bile acid and tryptase concentrations.

High-resolution manometry (*n* = 40) will be performed prior to randomisation and between 8 and 11 weeks of treatment, at two centres. Patients will fast overnight, then receive a tap water enema at 37 °C prior to endoscopically siting the manometry catheter, which is clipped to the mucosa of the splenic flexure. After 30 min of rest, the manometer will start recording for 4 h. At 2 h the patient will be given a meal to stimulate colonic contractions.

Barostat assessment (*n* = 80) will be performed prior to randomisation and between 8 and 11 weeks of treatment, at four centres. Patients will fast overnight, then receive a tap water enema at 37 °C prior to digital insertion of a barostat rectal compliance balloon. The bed will be tilted 15° head down to reduce abdominal visceral pressure on the rectum. After calibration the balloon will be inflated in increments of increased pressures, during which time patients will respond with their corresponding sensation of no sensation, first sensation, desire to defecate, urgency, discomfort, or pain. If the sensation of pain is reached the balloon is immediately deflated.

Six high-rectal biopsies will be obtained per patient (*n* = 80) either by endoscopy after siting of the colonic manometer or via rigid sigmoidoscopy after barostat assessment or at visit 3. Four biopsies will be snap-frozen and two will be placed in RNA later prior to freezing at − 80 °C before being analysed for mucosal 5HT and TPH-1 mRNA.

### Data analysis

#### General considerations

All hypothesis tests will be two-sided with a 5% significance level. Methods to handle missing data are described for each analysis. Analysis and reporting will be in line with Consolidated Standards of Reporting Trials (CONSORT) [30]. As TRITON is a double-blind trial, the trial statistician will be blinded to treatment group allocation throughout the trial, until the database has been locked and downloaded for final analysis. Only the safety statistician, supervising trial statistician, back-up safety statistician, and authorised unblinded individuals at the CTRU will have access to unblinded treatment group allocation prior to final analysis.

#### Frequency of analyses

Outcome data will be analysed once only at the final analysis, although statistical monitoring of safety data will be conducted throughout the trial and reported at agreed intervals to the DMEC. Final analysis will take place 16 weeks after the last patient is randomised.

#### Endpoint analysis

All analyses will be conducted on the intention-to-treat population, defined as all patients randomised regardless of non-compliance with the intervention. The primary endpoint will be analysed per-protocol to indicate whether results are sensitive to the exclusion of patients who violated the protocol (e.g. those patients randomised but subsequently found to be ineligible). Primary and secondary analysis will be performed blinded to random allocation. Outcome measures will be analysed by regression models appropriate to the data type. Such analyses will be adjusted for randomisation minimisation factors: site, completion of manometry assessment, barostat assessment, and baseline values where applicable, age, and gender. Baseline characteristics will be summarised by randomised group.

#### Primary analysis

The primary analysis will compare the difference between treatment groups in the proportion of patients achieving the FDA-recommended endpoint at 12 weeks post-randomisation, using a logistic regression model adjusted for minimisation, age, and gender. Any missing data will be assumed missing at random (MAR) and imputed for the primary analysis. Odds ratios and corresponding 95% confidence intervals will be presented.

Sensitivity will be analysed to assess the impact of missing data on the treatment effect. This will include complete case analysis and alternatives to multiple imputation (e.g. pattern mixture modelling) if missing patterns suggest data are missing not at random.

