### Sample size

TRITON plans to recruit 400 patients from up to 24 sites across England and Scotland. This will provide 90% power at 5% significance to detect a 15% absolute difference between the randomised groups in the proportion of patients achieving the FDA-recommended [28] endpoint of a weekly response for pain intensity and stool consistency for at least 6 weeks of the 12-week treatment period. This difference (15%) is considered to represent the minimum clinically important difference. We have assumed a placebo response rate of 17%, as recently reported using this endpoint and allowed for a 15% attrition rate.

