#### Secondary analyses

The difference between the treatment groups in the proportions of patients with satisfactory relief of IBS symptoms at 12 weeks post-randomisation will be analysed using logistic regression models, adjusting for minimisation, baseline values, age, and gender. Odds ratios and corresponding 95% confidence intervals will be presented. Any missing data will be assumed MAR and imputed.

The differences between the two treatment groups in the continuous secondary endpoints at 12 weeks post-randomisation will be analysed using linear regression models, adjusted for the minimisation variables, baseline values where applicable, age, and gender. These endpoints are urgency of defaecation over the last month, stool frequency over the last month, number of days per week with at least one loose stool (BSFS > 5) over the last month, average stool consistency, number of days rescue medication used over 12 weeks, abdominal pain score, HADS depression and anxiety scores, SF-LDQ score, IBS-QOL score and subscales, and PHQ-12 and IBS-SSS severity scores. Treatment estimates and corresponding 95% confidence intervals will be reported. Any missing data will be assumed MAR.

The differences between the treatment groups in stool frequency, abdominal pain, and urgency of defaecation post-treatment, over weeks 13–16 post-randomisation, will be analysed using a linear regression model adjusted for minimisation factors, baseline values, and relevant baseline factors. Treatment estimates and corresponding 95% confidence intervals will be reported. Any missing data will be assumed MAR.

Exploratory analyses on the daily measurements (worst abdominal pain, loose stools, number of stools passed, consistency of stool, worst urgency, and use of loperamide) will be carried out using repeated measures models, which incorporate correlation between measurements from the same patient. SAS software version 9.4 will be used in the analyses of primary and secondary endpoints.

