#### Mechanistic studies

Mechanistic studies will be analysed blinded to the intervention allocation, by the site research fellow under supervision of the Chief investigator and local supervising PIs. The differences between treatment groups in changes in whole gut transit times, colonic motility measures (percent time of cyclical retrograde contractions and high-amplitude propagating contraction (HAPC) frequency), rectal compliance, and thresholds for urgency and pain measured using the barostat, faecal bile acid concentrations, and faecal tryptase will each be assessed by linear regression models. In addition, exploratory mediator analyses will explore whether treatment effects, in terms of changes in urgency or pain, are mediated through changes in faecal bile acids or protease. Exploratory subgroup analysis (tests of interactions) will be performed to investigate the effect of the presence of each specified single nucleotide polymorphism allele on response to treatment, using logistic regression with addition of an interaction term for the allele and treatment.

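### The primary model's covariate list omits baseline pain and baseline loose-stool days; the analysis stays valid, but a possible gain in power at almost no cost is forgone

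*Protocol article*

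**What the plan says.** Three places in the protocol article bear on the primary model.

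- **Endpoint analysis** gives a general rule for outcome measures: regression adjusted for the minimisation factors "and baseline values where applicable, age, and gender".
- **Primary analysis** gives its own list for the responder endpoint: "using a logistic regression model adjusted for minimisation, age, and gender". No baseline value is named.
- **Secondary analyses** describes the parallel logistic model, for satisfactory relief, as "adjusting for minimisation, baseline values, age, and gender".

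Under Primary outcome measure, a responder needs a fall of at least 30% from baseline in weekly average worst pain and a fall of at least 50% in loose-stool days, in at least 6 of 12 weeks. Under Participant timeline, a two-week diary before randomisation records both quantities, and Visit 2 checks each against an eligibility threshold. Under Randomisation, the balancing factors are site and participation in the mechanistic assessments.

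For the mechanistic endpoints, Mechanistic studies plans to assess "The differences between treatment groups in changes in whole gut transit times" and in the other measures by linear regression. It names no covariates.

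**The concern.** The two baseline values that define response are obvious candidates for prognostic covariates, and the design does not balance them. Scaling each patient's outcome to baseline does not adjust the comparison for baseline, because the chance of reaching a percentage threshold can still depend on the starting level. For example, if loose-stool days are counted as whole days, a patient starting at 2 days must reach 1 (a 50% fall), one starting at 3 must also reach 1 (67%), and one starting at 7 must reach 3 (57%).

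Two things are at stake. The first is precision: if baseline severity predicts response, leaving it out of the model forgoes power and leaves chance imbalance in severity uncorrected. The second is clarity. The general rule could be read as bringing baseline into the primary model, while the specific list reads as leaving it out. The covariate set of the main analysis should not depend on which sentence is taken to govern.

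**Working it through.** **Inputs.** General considerations: "All hypothesis tests will be two-sided with a 5% significance level". Sample size: "This will provide 90% power at 5% significance", to detect a "15% absolute difference between the randomised groups", with a placebo rate of 17% (so 32% on ondansetron) and 15% attrition. Trial design: 400 patients, 1:1.

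**Step 1: reproduce the plan's figure without covariates.** With pooled variance under the null and mean rate (0.17 + 0.32)/2 = 0.245:

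n per arm = [1.960 × √(2 × 0.245 × 0.755) + 1.282 × √(0.17 × 0.83 + 0.32 × 0.68)]² / 0.15² = (1.192 + 0.768)² / 0.0225 ≈ 171.

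Total 342, and 342/0.85 = 403 after rounding up. The unpooled formula gives 168 per arm and 396. The planned 400 therefore reproduces. With 400 × 0.85 / 2 = 170 analysed per arm, power is 89.9%. The stated power does not rely on baseline adjustment.

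**Step 2: power with the two baseline values added.** 4,000 trials were simulated per scenario, with 170 per arm, overall rates held at 17% and 32%, and two independent standard-normal covariates. Each trial was analysed by logistic regression with and without the covariates. The odds ratios per SD are assumed.

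| Odds ratio per SD, each covariate | Without | With | Gain (points) |
|---|---|---|---|
| 1.0 | 90.1% | 90.0% | about 0 |
| 1.25 | 90.0% | 90.3% | 0.3 |
| 1.5 | 89.7% | 91.8% | 2.1 |
| 2.0 | 90.0% | 93.5% | 3.5 |
| 2.5 | 89.9% | 95.3% | 5.4 |

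The simulation error of each power figure is about √(0.9 × 0.1/4000) = 0.5 points. A second simulation with 3,000 trials per scenario gave similar gains: 0.9 points at 1.35, 2.2 at 1.65 and 4.1 at 2.0.

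**Step 3: mechanistic endpoints, if baseline were left out.** Take equal variances at baseline and follow-up (set to 1) and correlation rho. The unadjusted change score has variance 2(1 − rho), and the baseline-adjusted outcome has variance 1 − rho². Their ratio is (1 − rho²) / [2(1 − rho)] = (1 + rho)/2, which is 0.65, 0.75 and 0.85 at rho = 0.3, 0.5 and 0.7.

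The manometry section plans on 17 patients and a standardised effect of 1. Reading this as 17 per arm and 1 SD of the change score, normal-approximation power unadjusted is Φ(1/√(2/17) − 1.96) = Φ(0.96) = 83%. Dividing the SD by the matching factor, with baseline included it is 95%, 92% and 89% at rho = 0.3, 0.5 and 0.7. The documents give no value of rho.

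**The case against.** The omission can be defended. Responder status has no baseline value of its own, so the general rule's proviso about applicability can reasonably be read as not reaching the primary model. The endpoint is already expressed relative to each patient's baseline, and nothing in the documents shows how strongly, or in which direction, baseline severity predicts a percentage-change response. If it predicts nothing, the gain is nil, as the first row of the table shows. Adding covariates also changes what is reported: the odds ratio is non-collapsible, so the adjusted estimate is conditional on baseline severity and differs from the one now planned. All of this stands. It limits the size of the point but does not remove it, because the two values are already in hand and the two sections do not settle whether they enter.

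Several stronger readings are tempting, and the documents do not support them.

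- *The baseline data go unused.* They define response and determine eligibility.
- *The trial loses power.* Step 1 shows about 90% without any adjustment, which is what the plan states.
- *The comparison is biased.* Omitting a prognostic covariate from a randomised comparison neither biases the test nor inflates its error rate.
- *All the secondary models adjust for baseline.* The continuous models do so only where applicable, and the exploratory repeated-measures models name no baseline term.
- *The mechanistic models exclude baseline.* That section is silent, and the general rule in Endpoint analysis can cover it. Analysing change is not itself a fault: regressing change on treatment plus baseline gives the same treatment estimate as regressing the follow-up value on the same terms.

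**Conclusion.** The point holds as one of efficiency and clarity. The primary model's list leaves out two pre-randomisation values that the endpoint is built on, while the general rule allows for baseline values and the parallel secondary logistic model names them. The planned analysis is valid and adequately powered as it stands. The forgone gain is about 0 to 2 points of power if each covariate has an odds ratio per SD of 1.5 or less, and about 3.5 to 5 points at 2.0 to 2.5. It rests on assumed prognostic strength, two independent covariates and the plan's own rates and attrition.

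The mechanistic part is secondary and conditional. Only if baseline were in fact omitted would precision suffer. Adjustment would then cut the variance by 15% to 35% for rho from 0.7 to 0.3, assuming equal variances. This would matter most in the manometry (n = 40) and barostat (n = 80) sub-studies.

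**What to change.** 1. In Primary analysis, add baseline weekly average worst pain and baseline days per week with a BSFS 6 or 7 stool, both as continuous covariates. This brings the list into line with Endpoint analysis. Carry both into the imputation model, which should contain every variable in the analysis model.
2. State there that the odds ratio is conditional on these covariates.
3. In Mechanistic studies, state that each model of change includes the baseline value of the same measure as a covariate.

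The change should be settled before unblinding. It needs no new data, visits or patients. Both baseline values are needed to confirm eligibility, so they should be essentially complete. The one real cost is that the reported odds ratio becomes a more conditional quantity, which is a further reason to fix the list in advance.

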#### Dose titration

Since the optimum dose varies widely from 4 mg on alternate days up to 8 mg t.d.s., we will start all patients on 4 mg daily and after 2 days contact them to adjust the dose, thus avoiding the complication of constipation. If stool consistency remains loose, patients will be asked to increase their dose in 4-mg steps every 2 days up to the maximum of 8 mg t.d.s. If stools become hard or there is no bowel movement on day 2, they will be asked to stop the drug for 1 day and recommence at a lower dose changing from 4 mg daily to 4 mg on alternate days. If stools still remain hard or infrequent, patients will be asked to reduce their dosage to 4 mg every third day. Patients will discontinue the trial in the unlikely event that their stool remains hard even at this low dose.

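### The missing-not-at-random analysis of the primary endpoint depends on a condition that the observed data cannot settle; it should always be run

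*Protocol article*

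**What the plan says.** In the protocol article, the Primary analysis section sets one rule for all missing primary outcomes: "Any missing data will be assumed missing at random (MAR) and imputed for the primary analysis". It makes no distinction by reason for missingness.

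The same section names two kinds of sensitivity analysis. One is a complete-case analysis, with no condition attached. The other is "alternatives to multiple imputation (e.g. pattern mixture modelling) if missing patterns suggest data are missing not at random". No criterion is given for when patterns would suggest this.

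Three other places bear on the point:

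- Endpoint analysis keeps all randomised patients in the analysis, so patients who leave early have missing weeks that must be imputed. It also plans a per-protocol analysis, aimed at protocol violations such as ineligibility.
- Sample size states that the trial "allowed for a 15% attrition rate", with no split by arm or reason.
- Dose titration describes a withdrawal route tied to a drug effect: "Patients will discontinue the trial in the unlikely event that their stool remains hard even at this low dose". The section on 5HT3 receptor antagonist sensitivity reports constipation in 2% of patients when the dose was titrated.

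**The concern.** MAR and MNAR differ only in how the unobserved outcomes are distributed, given what was observed. Any response rate among the missing patients is compatible with the same observed data, so no missing-data pattern can show which assumption holds. A condition of this kind leaves the decision to judgement after the patterns have been seen, and it may never be met.

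Nothing else in the plan fills the gap. The complete-case analysis also relies on missingness being unrelated to the unobserved outcome. If the imputation model used only the covariates of the analysis model, the two results would be close, and their agreement would say nothing about MNAR. The per-protocol analysis answers a different question. Safety analyses tabulates withdrawals from treatment by arm and reason, but does not link them to the handling of missing outcomes.

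At stake is the robustness of the only primary comparison. As written, the trial could report without any analysis showing how far the result depends on MAR.

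**Working it through.** **Inputs.** From Sample size: "TRITON plans to recruit 400 patients"; "90% power at 5% significance to detect a 15% absolute difference between the randomised groups"; "We have assumed a placebo response rate of 17" per cent, hence 32% on ondansetron; and 15% attrition. From General considerations: "All hypothesis tests will be two-sided with a 5% significance level". Allocation is 1:1, so 200 per arm.

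**The plan's own figure.** The two-proportion formula with pooled variance under the null is n = [1.960·√(2 × 0.245 × 0.755) + 1.282·√(0.17 × 0.83 + 0.32 × 0.68)]² / 0.15². It gives 171 per arm, 342 in total, and 342/0.85 = 403. With unpooled variance the result is 168 per arm and 336/0.85 = 396. Both agree with 400. Power with 170 observed per arm (200 × 0.85) is 0.899. The sample size is not in question.

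**Scenarios.** Let m be the missing share in an arm, p the response rate among observed patients and q the assumed rate among the missing. The arm's rate is p(1 − m) + qm. Assumptions: p is 17% on placebo and 32% on ondansetron, and attrition means a missing endpoint. The second is a simplification, since a patient who leaves late may already have a determined outcome. The documents give only 15% overall, so every unequal split is assumed.

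| Assumption about missing patients | Missing, placebo/ondansetron | Placebo | Ondansetron | Difference (points) | Odds ratio |
|---|---|---|---|---|---|
| MAR (q = p) | 15%/15% | 17.0% | 32.0% | 15.0 | 2.30 |
| All non-responders | 15%/15% | 0.85 × 17 = 14.45% | 0.85 × 32 = 27.2% | 12.8 | 2.21 |
| All non-responders | 10%/20% | 0.90 × 17 = 15.3% | 0.80 × 32 = 25.6% | 10.3 | 1.91 |
| All non-responders | 5%/25% | 0.95 × 17 = 16.15% | 0.75 × 32 = 24.0% | 7.9 | 1.64 |
| Ondansetron missing at placebo rate, placebo MAR | 15%/15% | 17.0% | 29.75% | 12.8 | 2.07 |
| Ondansetron missing at placebo rate, placebo MAR | 10%/20% | 17.0% | 29.0% | 12.0 | 1.99 |
| Ondansetron missing non-responders, placebo MAR | 15%/15% | 17.0% | 27.2% | 10.2 | 1.82 |
| Ondansetron missing non-responders, placebo MAR | 10%/20% | 17.0% | 25.6% | 8.6 | 1.68 |

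With all missing counted as non-response and 200 per arm analysed, power is 88% (15%/15%), 73% (10%/20%) and 50% (5%/25%).

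**Under a true null.** Suppose 17% respond in each arm and all dropouts are non-responders. Observed rates are then 0.17/(1− m).

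- Equal 15% dropout: 0.17/0.85 = 20.0% in both arms, so there is no spurious difference.
- Assumed 10%/20% split: 0.17/0.80 − 0.17/0.90 = 0.2125 − 0.1889 = 2.4 points. The standard error is √[0.20 × 0.80 × (1/180 + 1/160)] = 0.0435, a shift of about 0.54 standard errors. The two-sided rejection probability is about 0.084 against a nominal 0.05.

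**Hard-stool withdrawal alone.** Setting 2% of the ondansetron arm to non-response gives 0.98 × 32 = 31.36%, a difference of 14.4 points and an odds ratio of 2.23. The change is 0.6 points. Under the null, 2% withdrawal in that arm alone gives 0.17/0.98 − 0.17 = 0.35 points.

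**The case against.** The strongest reply is that the plan already foresees the problem. It commits to sensitivity analysis for missing data, names pattern mixture modelling, and tabulates treatment withdrawals by arm with reasons. Those tables cannot prove MNAR, but they could prompt a reasonable judgement that it is plausible, and an analysis plan could sharpen the condition. This shows that the MNAR approach was considered. It does not turn the condition into a rule that can be applied objectively, and the condition is what this document fixes.

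A second reply concerns size. The larger effects need an assumed excess of dropout on ondansetron, for which the documents give no support. With equal dropout the odds ratio, which is the reported measure, moves only from 2.30 to 2.21, and no false difference arises under the null. This stands, and is why the figures are given as a range.

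A reader might also infer that MAR imputation would credit constipated ondansetron patients as treatment successes, because their diaries before withdrawal show no loose stools. The documents do not support this. The article does not say whether the imputation model uses diary data from before withdrawal, a detail that normally belongs in the analysis plan. The endpoint also requires a pain reduction of at least 30%, so improvement in stool form alone does not make a responder. And the article calls such withdrawal unlikely.

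**Conclusion.** The concern holds as a badly fixed rule: the only analysis that addresses MNAR depends on a condition that observed data cannot settle, and the one unconditional missing-data sensitivity analysis does not test it.

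In the scenarios shown, the planned 15.0-point difference falls to between 12.8 and 7.9 points. The lower values rest on assumed unequal dropout, and all of them rest on treating the 15% attrition as missing endpoints. The type I error near 8% belongs to the assumed 10%/20% split only. Most of the exposure comes from general attrition. Withdrawal for hard stools is a foreseeable example with a small effect of its own.

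It would go too far to read the non-responder figures as the true effect, or to say that the primary analysis is wrong. Counting missing as non-response is one assumption among several, and intention to treat with MAR imputation is not shown to be biased here. The point is a should-fix.

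**What to change.** Delete the clause that makes the MNAR analysis conditional. In its place, pre-specify a pattern-mixture multiple imputation of the primary endpoint with a delta adjustment that can differ by arm, taken across a range to the tipping point. State that it is always run and reported beside the MAR result. Include missing counted as non-response as one scenario in the range. The complete-case analysis can stay, described as a check that does not address MNAR.

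If the analysis plan already contains such an unconditional analysis, it is enough to align this wording with it.

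The cost is a few lines of text and a little more programming. The robustness statement may turn out less favourable. No treatment-stopping rule is changed.
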